### Data analyses

Descriptive statistics of participants’ clinical and demographic characteristics and all study outcomes will be reported. The recruitment and retention rates will be computed to determine the feasibility of a full RCT. A future complete RCT will be deemed feasible if the recruitment rate is at least 50% and the retention rate is at least 50%. Response rates to questionnaires, follow-up rates, and intervention adherence rates will also be calculated to provide further evidence for the feasibility of a definitive RCT. For the secondary objective, we will compare the longitudinal quantitative outcomes at three-time points (before, at the middle, and after the interventions) using the paired t-test (for continuous variables) and McNemar’s test (for categorical variables), if the data are normally distributed. The non-normally distributed data will be checked using the Wilcoxon test.

Qualitative data will be analyzed using content analysis by the research team’s qualitative researchers. The team will develop a codebook based on the study objective and framework. The predetermined codes include acceptability, implementation, facilitators, barriers, and satisfaction. A qualitative researcher will code the transcripts once the final codes have been defined and agreed upon. Emerging codes can be added to the codebook during the analysis. After the analysis, a detailed description of the findings will be reported. The qualitative findings will inform the acceptability of the study and the strategies or best practices of the study protocol. All research data will be stored in a non-publicly open repository which can be accessed by the principal researcher only to protect participant confidentiality.

The core team for this research consists of nurses with expertise in cancer care. The principal investigator is a professor of nursing who will oversee the study and deliver the telecoaching intervention. The research team members include nurses working in academia and at the DNCC. The nurses at DNCC will help provide a list of patients who may be eligible. In addition, a medical oncology consultant will also be involved in the study implementation process.

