#### Secondary outcomes

*Sociodemographic and clinical variables*. We will use a questionnaire to collect participants’ sociodemographic data (i.e., age, education, marital status, employment, ethnicity, and religious affiliation). We will also obtain clinical data at baseline from the participant’s medical record, including gynecological cancer type and stage and cancer treatment details.

*Distress*. Distress is defined by the National Comprehensive Cancer Network (NCCN) as a multifactorial unpleasant emotional experience of a psychosocial, and or spiritual nature that may interfere with the ability to cope effectively with cancer, its physical symptoms, and its treatment [25]. The NCCN recommended that distress be recognized, monitored, and managed sufficiently and timely [25]. The NCCN Distress Management Panel also developed the Distress Thermometer (DT), which originated from Roth’s study [26], for the initial, middle, and final distress screening. The DT is a single-item rating scale from 0 (no distress) to 10 (extreme distress) [25]. Participants will be asked to choose the number that best describes the distress level they have experienced over the past week, which could be related or unrelated to cancer. Meta-analyses of studies conducted in Asia and non-English-speaking countries suggested that the optimal cut-off point of DT was four [27, 28]. Therefore, participants who score less than four on the DT are noted to experience mild distress, whereas a distress level of four or above indicates a clinically significant distress level [25]. The DT has been adapted and validated by plenty of studies assessing patients with different cancer types in various languages and countries [25], including Indonesia [29]. The Bahasa Indonesia version of DT, which the NCCN has also verified, will be used in this study to measure the distress level of the participants at baseline and follow-up at weeks 6 and 10.

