*Knowledge and practice regarding chemotherapy side effects*. At baseline and follow-up at weeks 6 and 10, the participants will be asked to indicate their knowledge about chemotherapy side effects, how they manage them, and whether they experienced those symptoms in the past week. These outcomes will be measured using the chemotherapy side effect questionnaire outlined by Almohammadi et al. [30]. The questionnaire consists of two subsets. The first part assesses participants’ knowledge of 16 common side effects of chemotherapy, such as nausea and vomiting, fatigue, diarrhea and constipation, mouth ulcers and sores, hair loss, and sexual issues [30]. Yes/no responses will be used in this part of the questionnaire. The second part has seven items to examine the practice of side effect management, for example, "I measure my body temperature" and "I avoid eating spicy or fatty foods." We create four-scale Likert responses (never, seldom, often, and always) in this practice questionnaire. In our prior work, these side effect-related questionnaires have demonstrated their validity and reliability (Cronbach’s alpha of 0.720 and 0.708, respectively).

*Self-efficacy*. Self-efficacy, posited by Bandura as a strong predictor of behavior, is conceptualized as the perceived capability to perform specific actions needed to achieve particular goals [31, 32]. Numerous studies have shown the role of self-efficacy in improving self-management among patients with chronic diseases, including cancer [33, 34].

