The self-efficacy for managing chronic disease 6-item scale (SEMCD6) initially developed by the Stanford Patient Education Research Center will be used to measure the participants’ self-efficacy at baseline, week 6, and week 10. This questionnaire is brief and easy to administer as it only contains six items with a Likert scale ranging from 1 (not at all confident) to 10 (totally confident) to indicate how confident a patient is in managing the disease symptoms [35]. The scale’s total score is the mean score over at least four of the six items. A higher score indicates a higher level of self-efficacy. The original version of this SEMCD6 was proven valid and reliable in patients with chronic diseases [35]. Previous studies have shown satisfactory psychometric properties of the several versions of SEMCD6, e.g., Spanish, German, Swedish, and Portuguese [36–38]. This study has assessed the validity and reliability of the Bahasa Indonesia version of SEMCD6. The Cronbach’s alpha value of the SEMCD6 Bahasa Indonesia version is 0.813.

*Sexual quality of life (SQoL-F)*. Sexual quality of life is the primary outcome of our future RCT and will be measured at baseline, week 6, and week 10 using the Sexual Quality of Life-Female (SQOL-F). SQOL-F was initially designed by Symonds, et al. using data sets from women’s health surveys in the United Kingdom and the United States to examine how female sexual dysfunction impacts women’s sexual quality of life [39]. This tool comprises 18 questions that capture sexual self-esteem, emotional well-being, and relationship issues in women. Each item is rated on a six-point Likert scale ("completely agree" to "completely disagree"). Questions 1, 5, 9, 13, and 18 have reversed scoring. Therefore, the total score ranges between 18 and 108. A higher score indicates a higher quality of sexual life [39].

SQOL-F has been translated into some languages, for example, Iranian [40], Portuguese [41], Turkish [42], and Indonesia [43]. In the prior work of this study, the Bahasa Indonesia version of SQOL-F is valid and reliable (Cronbach’s Alpha = 0.751) among Indonesian gynecological cancer survivors.

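### Outcomes measured at three visits are compared with two-visit tests: women lost after week 6 leave the baseline-to-week-10 change, and five scores give 10 to 15 tests with no main contrast stated

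*Protocol article*

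**What the plan says.** Under Data analyses: "we will compare the longitudinal quantitative outcomes at three-time points (before, at the middle, and after the interventions) using the paired t-test" for continuous variables, with McNemar's test for categorical ones. Then: "The non-normally distributed data will be checked using the Wilcoxon test".

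Under Secondary outcomes, every score is taken three times:
- Distress Thermometer: the plan will "measure the distress level of the participants at baseline and follow-up at weeks 6 and 10".
- Side-effect knowledge and side-effect practice, two separately scored parts, on the same schedule. Participants will "indicate their knowledge about chemotherapy side effects, how they manage them, and whether they experienced those symptoms in the past week".
- SEMCD6: "self-efficacy at baseline, week 6, and week 10".
- SQOL-F, named as the primary outcome of the future RCT: it "will be measured at baseline, week 6, and week 10".

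The Sampling section sets 30 participants and expects them to supply preliminary effect sizes. Data analyses calls a full RCT feasible if recruitment reaches 50% and "the retention rate is at least 50" per cent. The article does not say which visit pairs are compared or which comparison is the main one.

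**The concern.** The named tests do not match the data structure. A paired t-test, a Wilcoxon signed-rank test and McNemar's test each take one pair of visits. This has two consequences.

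First, a woman who gives baseline and week-6 data and then leaves contributes nothing to the baseline-to-week-10 change. Participants are on chemotherapy and the Discussion expects some to drop out. If those who are doing worse leave more often, the change among those who remain is too favourable, and there is no control arm to expose it. That change is also the natural source of the SQOL-F effect size for the future RCT.

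Second, splitting three visits into pairs multiplies the tests, and the text does not say which one carries the answer.

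**Working it through.** The plan gives no alpha, SD, within-patient correlation or drop-out mechanism, and 30 rests on a citation, so there is no planned figure to reproduce. Everything below that is not a count is an assumption.

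**Number of tests.** Five scores (distress, knowledge, practice, self-efficacy, SQOL-F).
- Changes from baseline only: 5 × 2 = 10.
- All visit pairs: 5 × 3 = 15.

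**Chance of at least one false positive**, two-sided 0.05 per test. If independent, it is 1 − 0.95^k. The tests are correlated, so this was also simulated (30 women, complete data, visit correlation 0.5, between-score correlation 0 to 0.5, 6,000 runs).

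| Tests | Independent | Simulated |
|---|---|---|
| 15 | 1 − 0.95^15 = 53.7% | 41-49% |
| 10 | 1 − 0.95^10 = 40.1% | 32-38% |
| 5 (one overall time test per score) | 1 − 0.95^5 = 22.6% | 20-23% |

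The last row is what remains after moving to one model per score.

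**Who is lost.** At 50% retention, 15 of 30 reach week 10. If all 15 losses come after week 6, baseline to week 6 keeps 30 pairs and baseline to week 10 keeps 15.

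**Precision.** The variance of a paired change is 2(1 − ρ)/pairs in SD² units. It was compared with the generalised-least-squares variance using every observed visit, with equal visit correlations ρ of 0.3 to 0.7. Ratios (paired / model) for baseline to week 10:
- Visit counts 30/30/15: 1.17 to 1.24. For baseline to week 6 the ratio is 1.00, so there is no gain there.
- Visit counts 30/22/15: 1.14 to 1.23.
- Visit counts 30/27/24: 1.05 to 1.08.

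**Bias among completers when the true change is zero.** Let Y0, Y6, Y10 have SD 1 and assumed correlations r(0,6) = 0.5, r(6,10) = 0.7, r(0,10) = 0.4, with higher scores better. Let C = Y10 − Y0 and let m be the amount by which completers' mean on the drop-out driver exceeds that of all women.
- Driver is the change to week 6, D = Y6 − Y0. Var(D) = 2(1 − 0.5) = 1. Cov(C, D) = 0.7 − 0.4 − 0.5 + 1 = 0.8. Bias = 0.8m.
- Driver is the week-6 level. Cov(C, Y6) = 0.7 − 0.5 = 0.2. Bias = 0.2m. With equal correlations this covariance is zero, and so is the bias.

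For a logistic probability of staying with slope 1 per SD, m = 0.181 at 79% retention and 0.413 at 50%. With slope 1.5, m = 0.237 and 0.530.

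| Driver | Slope | 79% retained | 50% retained |
|---|---|---|---|
| Worsening to week 6 | 1 | 0.8 × 0.181 = 0.14 SD | 0.8 × 0.413 = 0.33 SD |
| Worsening to week 6 | 1.5 | 0.8 × 0.237 = 0.19 SD | 0.8 × 0.530 = 0.42 SD |
| Week-6 level | 1 | 0.2 × 0.181 = 0.04 SD | 0.2 × 0.413 = 0.08 SD |
| Week-6 level | 1.5 | 0.2 × 0.237 = 0.05 SD | 0.2 × 0.530 = 0.11 SD |

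Simulations with 30 women agree. Under the milder worsening-driven setting the spurious improvement was about 0.15 SD and 0.34 SD, with false-positive rates near 10% and 20%. A likelihood-type estimate from all observed visits had bias below 0.02 SD throughout.

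**The case against.** The best defence is that these are secondary outcomes of a small single-arm pilot. The go/no-go rule uses recruitment and retention only, and no decision hangs on these p-values. A journal article may also leave alpha, adjustment, choice of visit pairs and missing-data rules to a fuller document. All of this stands, and it limits the severity. It does not rescue the choice of test, because the article itself names two-visit tests.

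Several stronger readings are tempting but not supported:
- *The plan discards everyone who misses a visit.* It does not. Exclusion is pair by pair, and a woman lost after week 6 still counts in baseline to week 6.
- *The plan makes 15 unadjusted tests.* The article does not say which pairs are tested, so 10 is as compatible with it as 15. It is silent on adjustment, which is not a statement that there will be none.
- *A repeated-measures model cures multiplicity.* Five scores remain, at about 20-23%. Only designation of a main contrast and reporting as estimation deal with that, and such reporting would also be possible with paired changes.
- *A bias of a third of an SD should be expected.* That figure needs 50% retention, which is a minimum threshold and not a forecast, and drop-out driven by observed worsening. At 79% retention the 0.15 SD is smaller than the standard error of the change: √(2 × 0.6/24) = 0.22 SD for 24 pairs at correlation 0.4.

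The bias settings are all missing at random, which favours the model. Drop-out that depends on unseen values was not examined. Nor was the small-sample behaviour of an unstructured REML fit with as few as 15 women at week 10.

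**Conclusion.** The point holds in a limited form. The plan fixes two-visit tests for five scores measured at three visits, so the baseline-to-week-10 change rests on completers of that pair, and no main contrast is stated.

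The precision lost is modest: the paired variance is about 5-24% larger for baseline to week 10. Bias ranges from nil to about a third of an SD, or somewhat more with a steeper drop-out model, depending on correlations and a drop-out mechanism that the documents do not give. The familywise figures assume 0.05 per test.

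The reason to act is that these data are meant to supply preliminary effect sizes, including one for the future RCT's primary outcome. The alternative is valid under missing at random. It would not make a single-arm before-after change attributable to the intervention.

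**What to change.** Rewrite the secondary-outcome paragraph of Data analyses as follows:
- For each continuous score, replace the paired tests with one likelihood-based linear mixed model over all enrolled participants: visit as a categorical factor, unstructured covariance, REML, small-sample degrees of freedom. Name in advance the simpler covariance to use if it does not converge. Do not use classical repeated-measures ANOVA, which drops every woman with any missing visit.
- Make baseline to week 10 the main contrast, with week 6 supportive.
- For any dichotomised outcome, such as distress at the cut-off of four, use a corresponding repeated-measures logistic model in place of McNemar's test.
- Keep the Wilcoxon test as a sensitivity analysis for clearly non-normal scores.
- Report mean changes with 95% CIs as exploratory estimates, not tests of efficacy. State the missing-at-random assumption and give the number observed at each visit.

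The cost is a few sentences and slightly more complex analysis and reporting. No new data are needed.

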### Compensation

Participants will receive an internet data plan worth IDR 100,000 per month for the 2.5-month of the research activities. Additionally, a compensation of IDR 100,000 will be provided to each participant at the end of the FoRSHE-X digital intervention to offset the time spent in this study. Furthermore, the participants who will also be interviewed after the provision of digital education will receive IDR 100,000 each as compensation for transportation and time used during the interview process.

## Discussion

This study will examine whether a definitive trial to evaluate the potential benefits of the FoRSHE-X intervention that combines digital education and nurse-led telecoaching is viable and how it should proceed. Feasibility comprises the practicability of implementing the trial, including participant recruitment and retention, intervention delivery, and data collection. This study will also seek to determine appropriate and acceptable outcome measures to be included in the full RCT. As such, the intervention will be given to everyone who participated in this feasibility and pilot study. Nevertheless, using this approach, we cannot test the randomization strategy for the subsequent RCT.

The FoRSHE-X digital intervention is expected to enhance the self-efficacy of gynecologic cancer survivors in preventing and addressing communication obstacles that may hinder them from continuing therapy and preparing for the post-treatment period. This intervention can connect patients inquiring about information and psychological support from healthcare teams without space and time constraints. Digital technology is believed to expand the healthcare coverage and enhance patient participation in their sustainable self-care. The FoRSHE-X digital intervention has the potential to meet the supportive care needs of gynecologic cancer survivors undergoing chemotherapy. Therefore, the final findings of this pilot are planned to be published and disseminated to the participants, healthcare professionals, and other relevant groups. Anonymous data sets will be included in the publication.

Exploring the participants’ perspectives and experiences will also provide valuable insights into the acceptability of the study among cancer survivors who seek care. We will assess how well the FoRSHE-X intervention was received and whether participants found it suitable and beneficial. Potential challenges, uncertainties, and strategies to improve them will also be explored by the participants, including those who drop out of the study. The qualitative part of the study can also help identify other potential impacts of the intervention and its interaction with the context in which it is implemented.

Study participants being recruited only from one hospital may limit the generalizability of the results. In this situation, the research findings will likely predominantly reflect the characteristics and experiences of the individuals involved in the study. As a result, the findings might not be readily applicable to a population that is more diverse or geographically separated, such as people who reside in rural areas with little access to online resources. Rural communities often face particular difficulties in accessing healthcare services and digital technology, which may substantially impact how they respond to telehealth like the one under study. Consequently, while the results may be insightful for the hospital’s patient population, they should be considered relevant to a larger, more diverse population, especially those with limited internet access and lower educational levels.

One of the primary outcomes will be the sexual quality of life. Using telecoaching to improve the sexual quality of life for participants and their spouses can be a promising approach, although it may come with several concerns. Firstly, discussions about private matters may give rise to privacy issues, limiting participants’ openness and willingness to engage fully in telecoaching sessions. Secondly, participants in coaching programs often encounter various challenges in implementing the coaching recommendations effectively.

One potential major challenge is the resistance to change, as people tend to be more comfortable with their existing mindset and habits. Skills and patience may be needed to overcome such resistance. Thirdly, environmental or resource constraints can be another challenge for this study. Particularly for those living in suburban or rural areas, technological obstacles like poor internet connectivity may hinder effective and smooth communication during sessions. We will explore the participants’ perspectives to address the potential challenges of the trial.

This study is expected to improve healthcare access for cancer patients; so, they can complete their treatment. Following this study, the survivors are allowed to gain knowledge for self-care in solving chemotherapy side effects issues and psychological uncertainty through digital companionship anywhere. If the project is successfully supported by the survivors, the utilization of telehealth in increasing health literacy and self-efficacy of cancer patients in Indonesia might be adopted to improve well-ness of other patients with chronic illnesses. This feasibility research will improve web-based chronic disease management in future studies.

## Conclusion

To conclude, our research project is targeted to level up cancer survivors’ knowledge and ability to manage their physical and psychological issues during chemotherapy and successfully finalize the therapy. A digital supporting package of education and telecoaching for gynecological cancer survivors will be initially delivered to open the opportunity for these women to receive continuous care in their living environment. The pilot findings will assist in shaping future wider research and practice, with the long-term objective of incorporating telehealth into clinical practices across Indonesia to enhance cancer survivorship.
